### Statistical methods

Statistical analysis of study outcomes will be conducted using an intention-to-treat approach, meaning all HSOs will be analyzed in the group they were randomized to regardless of whether they receive the exploration facilitation strategy. The primary effect to be estimated for each outcome is its difference between the three study groups (distributing educational materials only, distributing educational materials plus exploration facilitation, and immediate exploration). Prior to estimating effects between these groups, balance on demographic characteristics, HSO characteristics, and other background covariates will be assessed by estimating propensity scores between the immediate exploration group and the combination of the two randomized groups (which may have substantial differences), and between the two randomized groups (which should not have differences if randomization worked as expected). If substantial imbalance is observed, doubly robust effects will be estimated by including both propensity score weights and including aforementioned covariates in the models described next.

Since they were not randomized, the comparability between the distributing educational materials only condition participants and the immediate exploration participants will be evaluated prior to propensity score estimation. Comparison of the distributing educational materials plus exploration facilitation group and distributing educational materials-only control group are causal due to the randomization, while comparison of either of these groups to the immediate exploration group is subject to selection bias. However, this selection bias is in itself interesting, and the analysis results will be used to understand what predicts immediate engagement. Each outcome’s distribution will be assessed to ensure adequate distributional assumptions are made in statistical modeling. If outcomes exhibit strong floor and/or ceiling effects, they can be rescaled to a proportion scale and modeled with zero- and/or one-inflated beta regression [19, 43]. If the missing data analyses uncover issues that should be addressed, we will use either full information maximum likelihood or multiple imputation [42]. In addition, summary statistics will be calculated for individual-level follow-up survey data and usage data for Tour of MI, LYSSN, and SIMmersion.

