**Methods:**

Using a multi-cohort cluster-randomized adaptive parallel-groups superiority experiment design, our aim is to test the effectiveness of augmenting a standard distributing educational materials dissemination strategy with a brief exploration facilitation dissemination strategy to support implementation of a motivational interviewing-based brief intervention. For each rollout, HSOs not responding to the distributing educational materials strategy will be randomized to either (a) receive no further intervention or (b) receive the exploration facilitation strategy. Assessed 4-months post-dissemination, the primary dissemination outcome is organizational-level adoption/preparation of the intervention (i.e., 1 + HSO staff downloads the manual and/or enrolls in the online asynchronous training). The secondary dissemination outcome is organization-level exploration of the intervention (i.e., 1 + HSO staff opens the dissemination email).

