#### Distributing educational materials

All HSOs begin in the distributing educational materials condition and receive the MOTIVATE CHANGE dissemination email (see Supplemental File 1), which has been designed to deliver three key messages: 1) SUD is common among people with HIV; 2) the MIBI, which takes 15–30 min to deliver, reduces substance use; and 3) the study is offering no-cost access to training resources on the MIBI. The dissemination email was developed using feedback from the study’s guiding coalition comprised of experts in HIV and SUD. Rolling batches of HSOs will be constructed for study management purposes. For each batch, HSO staff will be initially emailed on Tuesday. If a staff member from the HSO does not enroll by Friday, a dissemination email reminder will be sent. Email recipients have approximately 30 days to engage with the study’s landing page and enroll in the study by clicking the email’s “Learn More and Enroll” button before their access to the landing page expires. A one-week run-in period will be used to determine the percentage of HSOs for which the distributing educational materials emails is sufficient to move at least one HSO staff from pre-exploration to exploration, defined as at least one staff opening either of the dissemination emails. HSOs with at least one staff member enrolling in the study during the run-in period will not be randomized and will be categorized as a separate group (“immediate exploration”).

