### Participant timeline, sample size, and recruitment

Figure 1 provides an overview of the participant timeline. Regarding sample sizes, we anticipate approximately 750 HSOs and 3,100 individual HSO staff will eligible and have the opportunity to enroll in the study. Regarding recruitment, HSO points of contact will be sent the initial dissemination email (see Supplemental File 1) via Salesforce in a staggered batch format of up to 180 HSOs in six separate batches. The dissemination email will link to a landing page with information about the study and MI. Participants may choose to click the “Learn More & Enroll” button and be directed to the REDCap (Research Electronic Data Capture) [41] study consent and demographics survey.

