#### Data management

Data will be extracted from the REDCap system to develop analytic datasets. Logical checks and descriptive analyses will be used to assess errors, inconsistencies, and outliers. As part of the data management process, all constructed variables will be produced (e.g., scale scores, total scores). Distributional properties of outcome variables will be assessed to inform decisions about statistical models. Documentation will be prepared to accompany archived copies of the data. Finally, patterns of missing data will be evaluated. If there is evidence that data are not missing completely at random [42], methods for addressing missing data will be used as described in the section on statistical methods.

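### Covariate adjustment of the randomized comparison depends on an undefined imbalance trigger; one adjusted primary analysis should be fixed instead

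*Protocol article*

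**What the plan says.** The rule is in the Statistical methods section of the protocol article. The first step comes before any effect is estimated: "balance on demographic characteristics, HSO characteristics, and other background covariates will be assessed by estimating propensity scores". This is done twice, once for the immediate-exploration group against the two randomized groups combined, and once "between the two randomized groups (which should not have differences if randomization worked as expected". The consequence follows: "If substantial imbalance is observed, doubly robust effects will be estimated by including both propensity score weights", together with the same covariates in the outcome models. The article gives no measure of imbalance, no cut-off and no named covariate set.

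Three facts exist for every randomized HSO before allocation:

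- **Number of staff addresses emailed.** Addresses are collected from organizational websites and validated before launch (Eligibility criteria).
- **Any email opened in the one-week run-in.** Opening is recorded (Distributing educational materials). Only HSOs with an enrolled staff member are kept out of randomization (Allocation), so HSOs that opened but did not enroll are randomized.
- **Batch.** Emails go out "in a staggered batch format of up to 180 HSOs in six separate batches" (Participant timeline, sample size, and recruitment).

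None of the three is named in the analysis text.

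**The concern.** For the comparison with the immediate-exploration group, checking balance and then weighting is reasonable, because that group selects itself. For the two randomized arms the same logic does not apply. The article itself says these arms should not differ, so an observed difference is chance and does not show that correction is needed. A covariate is worth adjusting for when it predicts adoption, whether or not it happens to be balanced.

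Two consequences follow. First, the trial's main estimate is not fixed: it is either a simple contrast or a weighted and covariate-adjusted one, and an unstated cut-off decides which. Second, when balance looks acceptable, the rule leaves out information that the study already holds on every HSO. Number of addresses emailed is the clearest case. The organization-level outcome is met when at least one staff member adopts, so its probability rises with the number of staff contacted.

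**Working it through.** The article states no power, alpha or target effect, so there is no design figure to reproduce. Its projections do check: 0.35 × 750 = 262.5 (given as 263), and 0.02 to 0.03 × 750 = 15 to 22.5 (given as 15 to 23).

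**1. How far the missing cut-off decides the analysis**

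If 2-10% of the 750 HSOs enroll in the run-in (assumption), 735 to 675 are randomized, or about 367 to 337 per arm. Under sound randomization a standardized mean difference (SMD) has standard error √(2/n): √(2/367) = 0.074 and √(2/337) = 0.077. The chance that one covariate exceeds 0.1 is 17.6-19.4%, exceeds 0.2 is 0.7-0.9%, and exceeds 0.25 is 0.07-0.12%. For k independent covariates, the chance that at least one is flagged is 1 − (1 − p)^k:

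| Cut-off on SMD | 3 covariates | 5 covariates | 10 covariates |
|---|---|---|---|
| 0.1 | 44-48% | 62-66% | 86-89% |
| 0.2 | 2-3% | 3-5% | 7-9% |
| 0.25 | 0.2-0.4% | 0.4-0.6% | 0.7-1.2% |

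This is an illustration. The any-covariate rule, the covariate counts, independence and complete covariate data are all assumptions.

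**2. Staff count and the outcome**

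The mean is 3,100 / 750 = 4.13 addresses per HSO. If adoption is 3% at that mean and staff act independently, the per-staff rate is 1 − 0.97^(1/4.13) = 0.00735. HSO-level adoption, 1 − (1 − 0.00735)^m, is then 0.7% with 1 address, 2.9% with 4, 5.7% with 8 and 8.5% with 12.

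**3. What the rule does to error and precision**

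Simulation: 4,000 trials per scenario, 700 HSOs allocated 1:1, risk difference by linear regression with robust standard errors, two-sided 0.05. Assumptions: 35% of HSOs open in the run-in, mean about 4.1 addresses, adoption odds proportional to address count, odds ratio 4 or 10 for opening, no batch effect, treatment odds ratio 1 or 2.5. The adjusted model contained opening, log address count and five batch indicators.

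Type I error (Monte Carlo standard error 0.34 points):

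- always adjusted: 4.8-5.3%
- adjusted only if any SMD exceeds the cut-off: 4.7-5.2%
- smaller p-value of the two analyses taken: 5.9-7.3%

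The trigger fired in about 75% of trials at a cut-off of 0.1 and about 5% at 0.2.

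| Control adoption | Unadjusted variance larger by | Power at odds ratio 2.5, unadjusted v always adjusted |
|---|---|---|
| 3% | 2-7% | 66.1% v 67.7% (opening odds ratio 4); 62.0% v 64.6% (10) |
| 8% | 6-19% | 92.4% v 94.1% (4); 88.7% v 93.1% (10) |
| 16% | 23-29% | 95.5% v 98.8% (10) |

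At 3%, the variance ratios of 1.024 to 1.074 are worth 700 × 0.024 = 17 to 700 × 0.074 = 52 HSOs.

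**4. How many covariates the events can carry**

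At 3% in both arms, 0.03 × 700 = 21 events. Treatment, opening, log address count and five batch indicators make 8 parameters, or 21/8 = 2.6 events each. Without batch there are 3 parameters, or 21/3 = 7 events each.

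**The case against.** The strongest defense is that the check looks at covariates only and is placed "Prior to estimating effects between these groups", so nobody chooses an analysis by its result. That stands, and the simulation bears it out. A reader might infer that the rule inflates false positives. The documents do not support this: inflation appeared only when the analyst was assumed to take the smaller p-value, and nothing in the article proposes that. The Data management section does say "Distributional properties of outcome variables will be assessed to inform decisions about statistical models", but that is separate from the balance trigger and does not mention comparing arms.

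Second, the metric, the cut-off and the covariate list may sit in an analysis plan that is not shown, and the open category of other background covariates could include the three variables. This also stands, so their absence from the article is not the point. A separate plan could supply a cut-off, but adjustment of the randomized arms would still be conditional on imbalance, and that condition is stated in the article.

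Third, a reader might infer that strong predictors are being discarded and that the analysis ignores a design stratified by rollout. Only address count has a documented link to the outcome. The strength of run-in opening is an assumption, and nothing shows that batch predicts adoption. The abstract says "For each rollout, HSOs not responding to the distributing educational materials strategy will be randomized", but this describes timing. Batches exist for management ("Rolling batches of HSOs will be constructed for study management purposes"), and the Allocation section describes one prepared table used row by row, with no stratification.

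Fourth, a reader might take the 86-89% in the first table as this trial's chance of switching. It is not. The article assesses balance through propensity scores, and the listed demographics come only from staff who consent and enroll, so they would not be available for all HSOs.

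**Conclusion.** The point holds in a limited form. The article makes adjustment of a randomized contrast depend on chance imbalance at an unset cut-off, so the primary estimate is not determined in advance. The illustration shows that plausible cut-offs could make adjustment nearly certain or nearly absent. Validity is not threatened if the rule is applied mechanically; an unset cut-off does leave room for choice.

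The precision cost is modest: unadjusted variance is about 2-7% larger at 3% adoption, close to the 2-3% that the Discussion projects for the initial strategy, and 6-19% larger at 8%. A reader might expect savings equal to well over a hundred HSOs. That requires adoption well above the projected 2-3% as well as strong predictors. All the precision figures rest on the assumed effects of opening and address count.

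**What to change.** For the two randomized arms, delete the imbalance trigger and fix one primary analysis of adoption: the HSO-level risk difference, always adjusted for log number of staff addresses emailed and any run-in open (yes/no). Obtain it by standardization after a named regression, with robust standard errors, and show the unadjusted difference beside it. Include batch only under a rule fixed beforehand for sparse events, such as a pre-specified grouping of batches; collapsing batches after seeing the counts would bring back a data-dependent choice. Keep balance tables between these arms as description only. Keep propensity-score weighting for comparisons with the immediate-exploration group.

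The covariate set is meant for adoption. For exploration, a run-in open may already count as the outcome, so that covariate needs separate thought.

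The cost is a few sentences and a few lines of code, using email records that the study already holds. The article reports that the experiment ended on 5/14/25, so the change should be dated, with a statement of whether outcomes by arm had been seen.

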### Ethics and dissemination

#### Research ethics approval

The MOTIVATE CHANGE dissemination experiment was reviewed and approved by The Ohio State University IRB (Protocol 2024B0200), under Federalwide Assurance No. FWA00006378 from the U.S. Department of Health and Human Services’ Office for Human Research Protections. Any protocol modification that affects study conduct, potential risks to participants, or safety of participants requires a protocol amendment, which will be submitted to The Ohio State University’s IRB for approval. No amendments will be implemented until IRB approval has been received.

#### Consent

Informed consent will be obtained from all study participants. The dissemination emails will direct potential participants to the study’s landing page, which will provide brief descriptions of the study. The page will outline access to Phase I resources, including the MIBI Manual and the Tour of MI, and to Phase II platforms, SIMmersion and LYSSN. If the individual clicks the “learn more & enroll” button, they will be directed to the consent form. The consent form will include information on participants’ rights, as well as details on the data to be collected, such as a brief baseline survey, analytics from the Tour of MI, LYSSN, and SIMmersion, and a four-month follow-up staff survey. Individuals who chose the “I consent” option will be enrolled in the study. For HSOs randomized to distributing educational materials plus exploration facilitation due to non-response to the dissemination email, a verbal consent script will be used before starting the exploration facilitation call; individuals who visit the study’s landing page after the facilitation call will receive the same consent process as those who accessed the landing page via the dissemination email. Individuals cannot participate in any aspect of the project without first providing informed consent.

#### Confidentiality

Data provided as part of the study are confidential and will not be shared with anyone outside the study team. Efforts to protect participant confidentiality include: (a) assigning a unique participant number that is only accessible to the Principal Investigator and research coordinators, (b) securely storing all study documents (i.e., on a password-protected server located in a secure building), and (c) not including any identifying information in presentations or publications of study findings. De-identified data will be retained electronically by The Ohio State University until the final publication of associated study papers. Associated learning platforms are permitted to retain de-identified data indefinitely to be used to improve the operation and functionality of their products.

#### Access to data

During the active data collection and analysis phase, access to data is restricted to the Principal Investigator, research coordinators, lead statistician, and statistical programmers. Following completion of the study and publication of primary findings, a de-identified dataset will be constructed for public access. This public access dataset will be archived in the National Addiction & HIV Data Archive Program.

#### Dissemination policy

Study findings will be disseminated regardless of whether or not the hypotheses are supported. The dissemination of findings will include presentations at professional conferences and publications in peer-reviewed scientific journals. To ensure the widest access possible, we will prioritize scientific journals with open access, which will also facilitate compliance with the NIH Public Access Policy. Additionally, the Principal Investigator will disseminate copies of presentations and publications to NIDA, HRSA, and AETCs.

## Discussion

Before evidence-based interventions are implemented in practice to improve health outcomes, they must first be successfully disseminated to and explored and adopted by service organizations and providers. This protocol paper describes the MOTIVATE CHANGE dissemination experiment, a national-level cluster-randomized adaptive parallel groups superiority experiment to test an exploration facilitation dissemination strategy as an adjunct to increase adoption/preparation (i.e., primary outcome) and exploration (i.e., secondary outcome) of an evidence-based MIBI for SUD beyond that achieved by an initial distributing educational materials strategy. In comparison to implementation research, there is a dearth of dissemination research, especially dissemination research experimentally testing dissemination strategies [25]. As such, MOTIVATE CHANGE helps address a significant gap in the current dissemination and implementation literature.

The MOTIVATE CHANGE dissemination experiment builds upon the hybrid effectiveness-implementation research experiments that our study team has completed, which support the MIBI as an effective intervention for helping address comorbid HIV and SUD [19, 44] and facilitation as a cost-effective implementation strategy for implementing the MIBI [38]. It also builds on our research to better understand the prevalence and negative impacts of comorbid HIV and SUD [3], the SUD-focused EBIs that are most promising for integration within HSO settings [16], and the strategies that are most promising for purveyors/intermediaries to use for supporting dissemination and implementation of SUD-focused EBIs in HSO settings [32]. Building on this program of research, the MOTIVATE CHANGE dissemination experiment will help us understand the current market viability/demand for the MIBI within HSO settings, which Proctor et al. [45] noted as a neglected concept in dissemination and implementation science, and the extent to which a brief exploration facilitation strategy can increase MIBI exploration and adoption/preparation beyond an initial distributing educational materials strategy.

Because training and technical assistance centers have limited resources for dissemination efforts, effective dissemination strategies that help them utilize their limited resources most efficiently are needed. The MOTIVATE CHANGE experiment’s adaptive design may help in this regard. By quantifying HSOs’ progress through exploration and adoption/preparation phases for the distributing educational materials strategy, results may help training and technical assistance centers to estimate how much change occurs in the very short-term (i.e., one week) versus a longer period (i.e., four months). Distributing educational materials via email invitations to web-based resources is a low-intensity strategy that should have minimal costs. Exploration facilitation has greater costs because of the time required for training facilitators and then delivering the strategy. However, some efficiency may be gained by targeting exploration facilitation to those HSOs for which distributing educational materials was insufficient, rather than offering exploration facilitation to all HSOs. Using an adaptive approach may save resources, which is important for training and technical assistance centers that often serve a large geographic region but have limited financial resources [46].

We estimate MOTIVATE CHANGE will disseminate the MIBI to approximately 750 HSOs. According to Rogers [14], “a six-month communication intervention might increase knowledge of an innovation on the part of 35% of the audience while influencing only 2 or 3% of the individuals to adopt the new idea” (p. 198). We may then expect our initial distributing educational materials strategy to lead to exploration by 263 HSOs (35% of 750) and adoption/preparation by 15 to 23 HSOs (2–3% of 750). Ideally, MOTIVATE CHANGE will achieve an overall MIBI adoption/preparation of 20% or more of the approximately 750 HSOs (*n* = 150), which Rogers [14] termed the “tipping point” and when reached may cause the rate of subsequent adoption/preparation to rapidly accelerate throughout the target audience. More realistically, however, MOTIVATE CHANGE will achieve MIBI adoption/preparation among only innovators and early adopters, which together represent the first 16% (2.5% innovators and 13.5% early adopters).

